### Randomization, blinding and treatment allocation

The orthopedic surgeon checks the inclusion criteria after surgery for definitive inclusion. To assign participants to either of the groups a randomization list is generated by a computer (www.randomization.com) using block randomization with a block size of 6. Pre-stratification is applied for the level of physical activity determined with the activity coaching system prior to surgery (< the median level or ≥ the median level). The median activity level was determined in a pilot of 10 consecutive patients. An independent secretary not involved in enrolling participants in the study prepares concealed, consecutively numbered, sealed, opaque envelopes. The envelopes contain papers indicating the allocated treatment. Participants will receive their envelope at the start of the home-based exercise program from another independent secretary who is not aware of the randomization sequence. Participants can open the envelope while with the physical therapist. Subsequently, the physical therapist will inform the trial coordinator (KH) about the treatment allocation. Patients are instructed not to tell the researcher which group they are randomized to during the follow-up measurements.

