### Baseline characteristics of participants

Evaluation of baseline characteristics provides insight into the generalizability of the study, the success of the randomization and any potential confounders. Baseline characteristics of participants collected preoperatively are: age (years), gender, BMI, activity level (activity diary), coping style (PAM), walking pattern (GALN), physical status (TUG, 2MWT, KOOS) and quality of life (SF-36). This is shown in the flow chart (Fig. 1).

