#### Primary and secondary outcomes

The analyses will be performed following the intention-to-treat principle. Between-group differences of the primary outcome measure (TUG) measured at baseline, two weeks, six weeks and three months will be analyzed using generalized estimating equations (GEE) with an exchangeable correlation structure. GEE is a longitudinal data analysis technique that is suitable for investigating the course over time of the outcome variable and comparing this overall effect between study arms [49, 50]. Because GEE can adequately handle missing values (<20%), no imputation technique is planned on beforehand.

The continuous secondary outcomes adherence to the activity level, 2MWT, KOOS, SF-36 and healthcare use will be analyzed in the same way using GEE as well.

Differences in the baseline measurements and baseline characteristics of the two groups could potentially act as confounders. Only when the regression coefficient of the intervention variable in the GEE model changes by at least 10% after adding these variables to the model will they be adjusted for in the analyses [48]. A *p* < 0.05 is considered statistically significant. Patients cannot be deprived from other kinds of care and exercises. Therefore, other types of care and exercises are registered and reported.

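### The 10% change-in-estimate rule lets the observed result choose the primary model, and neither baseline TUG nor the randomization stratum is guaranteed a place in it

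*Protocol article*

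**What the plan says.** Under Primary and secondary outcomes, the protocol article specifies "generalized estimating equations (GEE) with an exchangeable correlation structure" for TUG. It then says "Differences in the baseline measurements and baseline characteristics of the two groups could potentially act as confounders", and that they will be adjusted for "Only when the regression coefficient of the intervention variable in the GEE model changes by at least 10% after adding these variables". No variable is exempt from this condition and none is fixed in advance as a covariate. Continuous secondary outcomes are analysed in the same way.

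TUG is itself a baseline variable. Baseline characteristics of participants lists "physical status (TUG, 2MWT, KOOS) and quality of life (SF-36" among the values collected before surgery.

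On the design side, Randomization, blinding and treatment allocation states "Pre-stratification is applied for the level of physical activity determined with the activity coaching system prior to surgery", split at the median. The analysis text does not mention this factor. The list of baseline characteristics names "activity level (activity diary), coping style (PAM), walking pattern (GALN", which is activity from the diary and not from the sensor that defined the strata.

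**The concern.** A change-in-estimate rule is a tool for confounding in observational data. In a randomized trial, baseline differences arise by chance. Covariates are adjusted for because they predict the outcome or because randomization was stratified on them, and the choice is made before the outcome data are seen.

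This rule asks neither question. It asks how far a covariate moves the treatment estimate relative to that estimate. A small observed effect makes entry easy and a large one makes it hard. A strongly prognostic baseline TUG can therefore be dropped because the arms happened to be balanced on it or because the observed effect was large. At stake are the width of the primary confidence interval, agreement between the analysis and the stratified design, and a primary model that can be named before the data are seen.

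**Working it through.** **Inputs from the article (Sample size, Abstract).** SD 4.2; three follow-ups; correlation 0.4 between follow-ups; a 10% difference in TUG; 15% dropout; N = 110, 55 per arm. Threshold: p "0.05 is considered statistically significant", taken here as two-sided.

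**Not in the article, so assumed.** Power 80%. The TUG mean behind the 10% is not given, so the effect in seconds is back-solved. The baseline-to-follow-up correlation r is varied from 0.2 to 0.6, because the stated 0.4 applies to follow-ups only.

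**Step 1: the sample size.** With n per arm = 2(z_α + z_β)² × SD² × [1 + (T − 1)ρ]/T ÷ δ², T = 3 and ρ = 0.4, the bracket term is 1.8/3 = 0.6. The SD of a patient's follow-up mean is 4.2 × √0.6 = 3.253 s. Evaluable patients: 110 × 0.85/2 = 46.75, taken as 47 per arm. N = 110 can be neither reproduced nor refuted without a mean and a power. Solving for the effect gives δ = √[2 × (1.960 + 0.842)² × 3.253²/47] = 1.88 s.

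**Step 2: what baseline TUG is worth.** In units of SD², the follow-up mean has variance 0.6. After adjustment for baseline it is 0.6 − r². The variance ratio is (0.6 − r²)/0.6; at r = 0.4 it is 0.44/0.60 = 0.73. An unadjusted interval is then wider by √(0.60/0.44) = 1.17, about 17%.

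**Step 3: when the rule fires.** Adding baseline TUG moves the coefficient by b × Δx, where b is the fitted slope and Δx the difference in baseline means. The rule fires if |b × Δx| ≥ 0.1 × |Δy|, where Δy is the unadjusted effect. The right-hand side is the observed result.

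**Step 4: simulation.** 40,000 trials per scenario, 47 per arm, follow-up mean analysed with no adjustment, with the rule applied to baseline TUG alone, or always adjusted.

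| r | Variance ratio | Rule omits baseline TUG, 1.88 s | Rule fires, no effect | Power at 1.88 s: never / rule / always | Power at 0.94 s: never / rule / always | Type I error, rule |
|---|---|---|---|---|---|---|
| 0.2 | 0.93 | 70% | 73% | 79.2 / 80.8 / 81.6 | 28.2 / 28.8 / 29.6 | 0.048 |
| 0.3 | 0.85 | 54% | 84% | 79.0 / 83.2 / 84.8 | 28.3 / 30.3 / 32.1 | 0.044 |
| 0.4 | 0.73 | 42% | 89% | 79.1 / 87.6 / 89.4 | 28.8 / 33.9 / 36.7 | 0.043 |
| 0.5 | 0.58 | 34% | 92% | 79.2 / 93.0 / 95.1 | 28.5 / 39.6 / 44.0 | 0.043 |
| 0.6 | 0.40 | 29% | 95% | 79.2 / 97.4 / 99.2 | 28.1 / 52.0 / 58.7 | 0.043 |

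At r = 0.4 the same covariate enters in 89% of trials with no effect and in 58% at 1.88 s. That is the dependence on the result. Against always adjusting, the rule loses 0.8 to 2.1 points of power at 1.88 s and 0.8 to 6.7 points at half that effect.

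**Step 5: the stratum.** Sensor-measured preoperative activity is a baseline characteristic, so it falls in the class that the rule governs. Nothing else in the article puts it in the model. Its effect on precision was not quantified.

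**The case against.** The rule and its threshold are written down in advance, and the numbers above show limited harm. A reader might infer that picking the model from the result inflates false positives. It does not here: type I error under the rule is 0.043 to 0.048. A reader might also infer that the trial falls short of its planned power. The documents do not support that, because the stated sample size, as described, takes no credit for baseline adjustment, and power under the rule is above the unadjusted figure throughout. Nor does nearly any covariate enter when the effect is null: in a separate simulation of 2,500 trials at r = 0.4, about 3 of 8 pure-noise covariates were selected. These limits stand and set the size of the point.

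Two further objections stand in part. First, a journal article may leave the stratum to the full protocol or analysis plan, so its absence from the analysis paragraph alone would be no finding. But the article states a rule that covers all baseline variables, and an analysis plan that followed it would admit the stratum only conditionally.

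Second, the article analyses "Between-group differences of the primary outcome measure (TUG) measured at baseline, two weeks, six weeks and three months", so baseline TUG may already be in the outcome vector. Its role is not stated, and that reading does not rescue the plan as written. One group coefficient averaged over four occasions including baseline is diluted to about 3/4 of the follow-up effect. An unconstrained change-from-baseline contrast has variance 0.6 + 1 − 2 × 0.4 = 0.8 SD², against 0.6 unadjusted and 0.44 adjusted (all correlations 0.4).

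**Conclusion.** The point holds as one of precision and pre-specification that should be fixed; it does not threaten the trial's validity. The observed treatment estimate selects the primary model, and neither a prognostic baseline TUG nor the stratification factor is assured of inclusion.

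Always adjusting for baseline TUG would cut the variance of the effect by about 7% to 60%. The rule forgoes that gain in a substantial share of trials, although the average power cost is small because it omits baseline TUG mostly when the imbalance is small relative to the observed effect.

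The size rests on the assumed r, the assumed 80% power and the back-solved 1.88 s, and on a simulation of one covariate and the mean of complete follow-ups. The result-dependence itself needs none of these assumptions; it follows from the wording of the rule.

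**What to change.** Remove the 10% rule from the primary analysis. Specify in advance a GEE on the TUG values at two weeks, six weeks and three months, with group, visit, one named pre-randomization TUG value and the sensor-based activity stratum, whatever imbalance is seen. Use baseline TUG as a covariate and not as an outcome.

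State which TUG value is meant. Baseline characteristics of participants describes preoperative values, while Procedures and informed consent places the baseline measurement on day three to five after surgery. If the later value is chosen, confirm that it is taken before allocation is revealed.

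For secondary outcomes, adjust 2MWT, KOOS and SF-36 for their own baseline value and the stratum. Healthcare use is counted from the start of the exercise program, and percentage adherence is defined against that program, so neither has a baseline value of its own. Adjust both for the stratum, with preoperative diary activity as an optional covariate for adherence. Keep any further covariates for labelled sensitivity analyses.

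The cost is one paragraph of analysis text and two model parameters (one for TUG, one for the two-level stratum). No new data are needed. The change should be settled before outcomes are examined by group.

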#### Healthcare costs and cost-effectiveness

The total healthcare costs will be determined after one year and include all costs related to the TKA surgery measured by the healthcare insurance. The total costs are measured as a continuous variable over a period of 12 months. The cost-effectiveness will be analyzed based on group differences in healthcare costs (number of consultations and other healthcare use). The time off work or caregiver time off work is not measured. This economic analysis is based on the principles of a cost-utility analysis. The primary outcome measures for the economic evaluation are costs and quality-adjusted life years measured with the SF-36. The incremental cost-effectiveness ratio (ICER) “cost per quality-adjusted life years (QALY) gained” will be calculated. Uncertainty surrounding this ICER will be determined using a nonparametric bootstrap method. A cost-effectiveness acceptability curve will be extracted. The impact of uncertainty surrounding parameters of the ICER will be explored using one-way sensitivity analysis on the range of extremes.

In the quantitative process analysis we will calculate the correlation between the data registered in the activity diary (performed activities and the time spent on it) with the data from the activity coaching system and the usability of the activity coaching system using semi-structured interviews. The audio-records from the interviews will be transcribed verbatim and checked for accuracy by KH. Thereafter the transcripts will be analyzed using qualitative data analysis with an open-coding system [51]. Afterwards a thematic analysis will be used to get insight in the experiences of the participants with the program, the impact of the activity coach on adherence and the possible barriers and facilitators. These data will be used to generate possible hypotheses on mediating factors which can be tested using the quantitative data [52].

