### Activity coaching system in the intervention group

The home-based program is exactly the same for the intervention and the control group. The only difference is the addition of the digital activity coaching system in the intervention group. The intervention group wears the activity coaching system during the home-based exercise program for two weeks: After two weeks’ use, the influence of the activity coaching system seems to diminish because patients include exercises in daily routines as shown in patients with COPD [27]. Physical therapy after TKA is effective when it starts early [29], so we hypothesize that adding the activity coaching system in the first two weeks [30, 31] stimulates people towards a more active and healthy activity behaviour. It consists of an accelerometer-based activity sensor (Promove 3D, Inertia Technology, Enschede, the Netherlands), which is worn on the patient’s hip combined with a smartphone (Desire S; HTC, New Taipei, Taiwan). The activity coaching system is shown in Fig. 2 and consisted of a tri-axial piezoelectric accelerometer. The accelerometer measures accelerations in the anteroposterior, mediolateral and longitudinal axis of the trunk. The acceleration is band pass filtered, with cut-off frequencies at 0.11 and 20 Hz as described by Bouten et al. [32] and is used to remove the gravitational component from the accelerometer signals. These filtered signals are used to calculate the Integral of the Modulus of the Accelerometer output (IMA) values for the most recent 60 s. The IMA values as measure for physical activity are expressed as mean acceleration per minute and defined as counts per minute [32].

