The KOOS assesses function over the previous week and is composed of five subscales: pain, symptoms, activities in daily living, activities in sports and leisure, and knee-related quality of life [40–43]. Answers are given using a Likert scale ranging from 0 to 4. A normalized score (100 indicates no symptoms, and 0 indicates extreme symptoms) is calculated for each subscale. The KOOS has been shown to have excellent reliability and good content and construct validity when used for short- and long-term follow-up of knee injury [42, 43]. It has been validated for people with TKA and has been used to evaluate physical therapy outcomes [42, 43]. The KOOS is scored after two and six weeks, three months and one year.Quality of life (QoL), measured with the Short Form 36 (SF-36)

The SF-36 is a multipurpose, short-form health survey with 36 questions that measure eight domains of QoL (vitality, physical functioning, bodily pain, general health perceptions, physical role functioning, emotional role functioning, social role functioning and mental health). It has been shown to capture improvements in seven of its eight domains in patients after TKA in the first three months after surgery [44] and continues to indicate improvements in health-related QoL over the next six months [45]. In addition, the results of the eight domains have been combined into two summary scores: physical component score and mental component score [46]. The SF-36 is scored after two weeks, six weeks, three months and one year postoperatively.Healthcare use

Healthcare use includes all kinds of healthcare consumed by the patient in relation to TKA surgery beginning at the start of the home-based exercise program up to one year postoperatively. It includes physical therapy, hospital visits, visits of the general practitioner and medication use. The patient sign informed consent to ask for an overview of healthcare costs (health insurance, physical therapist) and patients report how much pain medication (paracetamol, NSAIDs) they use for their knee pain. The use of pain medication is asked about through a medication diary. Healthcare use is measured during the period up to one year after surgery.Adherence to the home-based exercise program (intervention group) measured with the accelerometer (activity coaching system)

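### The stated cost scope leaves out the coaching system, the one resource that differs by design between the arms, so the cost per QALY leans towards the intervention

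*Protocol article*

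**What the plan says.** In the protocol article, the section Healthcare costs and cost-effectiveness defines the cost total: "The total healthcare costs will be determined after one year and include all costs related to the TKA surgery measured by the healthcare insurance". It then states how the arms are compared: "The cost-effectiveness will be analyzed based on group differences in healthcare costs (number of consultations and other healthcare use", with the parenthesis closing there. One item is declared outside the measurement: "The time off work or caregiver time off work is not measured". The result is an incremental cost-effectiveness ratio (ICER) per QALY, with QALYs taken from the SF-36, a nonparametric bootstrap, an acceptability curve and a one-way sensitivity analysis.

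The healthcare-use paragraph under Secondary outcomes lists the components: "It includes physical therapy, hospital visits, visits of the general practitioner and medication use". Patients consent to the team's request to "ask for an overview of healthcare costs (health insurance, physical therapist", and a diary records pain medication. The window for healthcare use is "beginning at the start of the home-based exercise program up to one year postoperatively".

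The section Activity coaching system in the intervention group states that the home program is identical in both arms and adds: "The only difference is the addition of the digital activity coaching system in the intervention group". The system is a hip-worn sensor with a smartphone and an app that sends coaching messages.

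**The concern.** A cost-utility comparison needs, above all, the cost of what one arm receives and the other does not. Here that is the coaching system, and it appears in no cost list or named data source. The Discussion raises the possibility that the intervention reduces healthcare use. The plan would count such savings but not the outlay that produced them.

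Cost-effectiveness is a stated secondary objective. If the system is in effect treated as free, it can appear cost-saving or acceptable at a given willingness to pay when a full costing would not show this.

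**Working it through.** The article states no cost, QALY or ICER figure, so there is none to reproduce. The check has three steps.

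**1. Does any listed item capture the system?**

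| Item in the cost scope | Source | Captures sensor, phone and app? |
|---|---|---|
| TKA-related costs | Insurer overview | Only if billed to the insurer; not stated |
| Physical therapy | Insurer or therapist overview | No; at most set-up time, if billed as a consultation |
| Hospital and general practitioner visits | Insurer overview | No |
| Pain medication | Patient diary | No |
| Home trainer (not listed) | – | Not relevant: lent to both arms for two weeks, so its cost cancels |

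The activity measurement before surgery, used for stratification, precedes allocation. It is a trial measurement and does not offset the two weeks of intervention use.

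**2. What does the omission do?** Let ΔC be the true incremental cost per patient, ΔQ the incremental QALYs, and D > 0 the per-patient system cost that is not captured.

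- Incremental cost as planned = ΔC − D.
- ICER as planned = (ΔC − D)/ΔQ = true ICER − D/ΔQ. For ΔQ > 0 it is too low by D/ΔQ.
- Net benefit at willingness to pay λ: planned value = λΔQ − (ΔC − D) = true value + D. It is too high by D per patient whatever the sign of ΔQ, so the bias remains where the ICER itself is hard to interpret.

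**3. How large could it be?** Neither D nor ΔQ is in the document. Both are assumptions here, and the entries are D/ΔQ in euro per QALY.

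| D (assumed) | ΔQ = 0.005 | ΔQ = 0.01 | ΔQ = 0.02 | ΔQ = 0.05 |
|---|---|---|---|---|
| 50 | 10,000 | 5,000 | 2,500 | 1,000 |
| 200 | 40,000 | 20,000 | 10,000 | 4,000 |
| 500 | 100,000 | 50,000 | 25,000 | 10,000 |

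For example, 200/0.01 = 20,000. The range is 100-fold, so the table shows how the error scales and does not estimate it.

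**Would the planned uncertainty analyses reveal it?** No. The bootstrap resamples recorded costs, so a cost never recorded shifts every replicate, and with them the acceptability curve, by the same D per patient. The one-way analysis varies parameters of the ICER, and a cost that is not a parameter cannot be varied.

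**The case against.** The strongest reply is that the exclusion is inferred. No sentence says that the system is left uncosted, the verb used for the cost total need not introduce a closed list, and the only item declared unmeasured is time off work. A journal article commonly leaves unit prices and the costing of intervention delivery to a fuller document. The article also does not say who pays for the sensor, phone or app.

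Part of this stands. The conclusion must be conditional on the system not being billed to the insurer, and no size can be claimed. But the article does more than stay silent on prices. It states what the cost comparison rests on, namely "based on group differences in healthcare costs (number of consultations and other healthcare use" (the parenthesis closes there), and it lists the components of that use. Followed as written, this scope does not reach the system.

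It is also fair to say that this is the last of five secondary objectives, that the primary TUG analysis is unaffected, and that the cost can still be added at the analysis stage. These points limit the weight of the concern without removing it.

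Three stronger readings are tempting, and the document does not support them:

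- **Only insurer costs are counted.** The therapist overview and the medication diary are also named.
- **The cost section wrongly includes the operation and admission.** Its reference to surgery-related costs can be read under the healthcare-use definition, which starts at the home program. Any costs before randomization would in any case be balanced in expectation and so would not bias the comparison.
- **QALYs are compared without baseline adjustment.** The article nowhere commits to this. It is silent on covariates in the economic analysis.

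**Conclusion.** The concern holds in conditional form. The stated scope omits the only resource that differs by design between the arms. Unless the insurer is billed for the system, incremental cost is understated by D per patient and, for a positive QALY gain, the ICER by D/ΔQ, both in favour of the intervention.

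The direction follows from the text and from D being positive. The size is unknown, and the range of 1,000 to 100,000 euro per QALY rests wholly on the assumed inputs. A reader might infer that the trial's cost-effectiveness result is bound to be materially wrong. The document does not show this, because a cheap system or a large QALY gain would make the shift small. The point should be corrected before the economic analysis and has no bearing on the clinical outcomes.

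**What to change.** In Healthcare costs and cost-effectiveness, state that intervention-arm costs include a per-patient cost of the coaching system: sensor and smartphone spread over their expected number of uses, the app, and set-up and support time. Any therapist time already in the therapist's or insurer's overview should not be counted twice. If the insurer is in fact billed for the system, say so. Name this cost as one of the parameters in the one-way sensitivity analysis and give its range.

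The price is some costing work, a few sentences, and an ICER that may look less favourable. No further patient data are needed.

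Two optional additions are not corrections of error. The cost section could repeat the start of the cost window given under Secondary outcomes, as a wording alignment. Incremental QALYs could be adjusted for the preoperative SF-36 utility, as a refinement.

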### Procedures and informed consent

All eligible patients are informed about this study and are invited to participate by the orthopedic surgeon before surgery. The surgeon informs the researcher about patients possibly willing to participate. The researcher informs the patients by phone about the study and provides them with a patient information letter. Patients have one week to consider participating in the study. Patients who are willing to participate sign an informed consent form. After that, the researcher performs the preoperative measures and determines whether the patient is eligible. To minimize the patients’ load, the preoperative assessment is used as an inclusion criterion and preoperative measurement using overlapping tests. Five orthopedic surgeons perform the TKA surgeries. The number of TKA surgeries per year carried out by each surgeon varies from 50 to 70. After surgery, the definitive inclusion takes place if patients are going home after three days post-surgery and no complications are present. After the definitive inclusion, the baseline measurement and randomization take place. The baseline measurement is planned preferably for the third day, and at the latest for the fifth day. A flow chart is shown in Fig. 1. Subjects can leave the study at any time for any reason if they wish to do so without any consequences. The researcher will report serious adverse events to the accredited medical ethical review board of the Medisch Spectrum Twente community hospital in Enschede, the Netherlands, which approved the trial (registration number P15–09, NL52370.044.15). The researcher can decide to withdraw a patient during the study for urgent medical reasons, such as thrombosis, infections of the knee or other complications. KH is the coordinator of the trial and the other authors comprise the steering committee.

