### Sample size

The sample size is based on the primary outcome measure TUG. The sample size is determined using a longitudinal regression model with three follow-up measurement points (two and six weeks and three months). According to the formula described by Twisk [48] for longitudinal studies with repeated measures the required sample size is calculated assuming a mean effect of 10% difference for the TUG scores between the groups over time and a standard deviation of 4.2. These parameter values are based on a study by Kennedy et al. on the clinimetric properties of the TUG in patients with knee and hip arthroplasty [35]. We further assume a correlation coefficient of 0.4 for the correlation between the follow-up measurements. Assuming a dropout rate of 15% a total number of 110 patients is needed. The recruitment period is from 1 April 2015 to 1 August 2017.

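### The stated reason for not imputing is a property of GEE and does not carry over to the one-year QALY and bootstrapped ICER, which would by default omit patients who leave early

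*Protocol article*

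**What the plan says.** All places are in the protocol article.

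- **Missing data** (Primary and secondary outcomes): "Because GEE can adequately handle missing values (<20%), no imputation technique is planned on beforehand". The same section declares intention-to-treat and says that the continuous secondary outcomes, with SF-36 and healthcare use named among them, are analysed by GEE in the same way as the TUG.
- **Economic analysis** (Healthcare costs and cost-effectiveness): "The primary outcome measures for the economic evaluation are costs and quality-adjusted life years measured with the SF-36". On costs: "The total costs are measured as a continuous variable over a period of 12 months". The ICER per QALY gained gets a nonparametric bootstrap, an acceptability curve and a one-way sensitivity analysis. GEE is not mentioned, and neither is missing data. The abstract and the Objective section list cost-effectiveness as the fifth secondary outcome or objective.
- **Leaving the study** (Procedures and informed consent): patients may stop at any time. On withdrawal by the researcher: "The researcher can decide to withdraw a patient during the study for urgent medical reasons, such as thrombosis, infections of the knee". Further complications are allowed for as well.
- **Expected loss** (Sample size): "Assuming a dropout rate of 15% a total number of 110 patients is needed". This calculation uses three TUG follow-ups, the last at three months.
- **Cost sources** (the economic section and Secondary outcomes). On the total: "The total healthcare costs will be determined after one year and include all costs related to the TKA surgery measured by the healthcare insurance". On access to the records: "The patient sign informed consent to ask for an overview of healthcare costs (health insurance, physical therapist"). Pain medication is the exception: "The use of pain medication is asked about through a medication diary".

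**The concern.** GEE can use whatever visits a patient has, because each visit is a record in the model. A one-year QALY is a single quantity per patient that needs SF-36 values across the whole year, and the cost is a single 12-month total. For a patient who stops contributing SF-36 forms, a GEE on SF-36 scores still uses the early visits. A QALY calculated for that patient cannot be completed unless the later utilities are imputed or modelled.

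The article therefore makes a decision (no imputation) and gives one reason for it, and that reason does not hold for this analysis. If the text is followed as written, patients without a full SF-36 series drop out of the ICER. Costs that could have been recovered for them drop out too if the ICER is computed on patients with both components. The loss may well be informative, because the reasons named for withdrawal by the researcher are complications. At stake are the estimate for one secondary objective and its uncertainty: a bootstrap reflects sampling error among the patients it is given, not the selection that produced them.

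**Working it through.** **1. The plan's own figure.** The total is 110, or 55 per arm. It cannot be re-derived from the article, which gives neither the power nor the TUG mean to which the 10% effect applies. With SD 4.2, three follow-ups and correlation 0.4, the variance factor is (1 + 2 × 0.4)/3 = 0.60. At two-sided 5% and 80% power, a mean of 19 s (difference 1.9 s) needs 47 per arm, which gives 110 as 47 × 1.15 or 112 as 47/0.85, rounding up per arm. The figure is neither confirmed nor refuted, and nothing below depends on it beyond 110 and 15%.

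**2. Number affected.** Assume that the 15% set for three months also held at one year.
- Lost: 0.15 × 110 = 16.5. Retained: 0.85 × 110 = 93.5.
- At the 20% limit in the GEE sentence: 22 lost, 88 retained.

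**3. Complete SF-36 series.** There are four follow-ups: two weeks, six weeks, three months and one year. If retained patients also miss each form independently with probability m (an assumed range), the complete fraction is 0.85 × (1 − m)^4:

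| m | Fraction | Of 110 |
|---|---|---|
| 0% | 0.850 | 93.5 |
| 2% | 0.784 | 86 |
| 3% | 0.752 | 83 |
| 5% | 0.692 | 76 |

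**4. How much of the year one missed form removes.** The interval from three months to one year is 9 of 12 months. A patient followed to three months but not to one year has no closing value for 75% of the QALY period.

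**5. When omission biases the QALY difference.** Let p be the proportion lost in an arm and g the mean QALY of completers minus that of leavers, in SD units. The completer mean differs from the full-arm mean by p × g. The error in the between-arm difference is p_I × g_I − p_C × g_C, where I is intervention and C is control. The SE of a completer difference is about sqrt(2/46.75) = 0.207 SD, with 55 × 0.85 = 46.75 per arm. The documents give no value for g or for loss by arm, so these rows are illustrations only:

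| Loss, I / C | Gap, I / C (SD) | Error (SD) | Error / SE |
|---|---|---|---|
| 15% / 15% | 1 / 1 | 0 | 0 |
| 10% / 20% | 1 / 1 | −0.10 | 0.48 |
| 10% / 20% | 2 / 2 | −0.20 | 0.97 |
| 15% / 15% | 1 / 2 | −0.15 | 0.73 |

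Swapping the arms reverses each sign. Equal loss with equal gaps gives no error in the difference.

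**6. Costs.** Insurer and therapist totals come from records requested with signed consent, so they do not depend on attendance at study visits. Only diary medication necessarily stops when the patient stops.

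**The case against.** The strongest reply is that this is silence in a condensed article. The no-imputation sentence stands under the heading for primary and secondary outcomes, the economic evaluation has its own section and its own outcome measures, and a fuller protocol or analysis plan could set a rule for missing utilities. The intention-to-treat statement points away from dropping patients, and a bootstrap can resample incomplete records and re-estimate arm-level utilities each time. Patients with postoperative complications or a hospital stay over three days are also excluded before randomization, and later withdrawal is discretionary.

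Part of this stands. The lack of a detailed imputation model would not be a finding in itself, and restriction to completers is the default consequence of the text, not something it states. The omission argument does not dispose of the point, however. The article states a decision with a reason, applies it to the two inputs of the ICER (SF-36 and healthcare use), and lists cost-effectiveness among the secondary outcomes. The reason fails for the analysis described. The planned one-way sensitivity analysis concerns the parameters of the ICER and is not described as covering missing patients.

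A reader might infer more than the documents support:
- *That total cost is also lost for early leavers.* It is not, because the insurer and therapist records can still be requested where consent allows.
- *That a completer ICER must understate costs and overstate QALYs.* That might describe arm averages if leavers fare worse. The ICER uses differences between arms, and their bias depends on imbalance about which the documents say nothing.
- *That 15% is the expected one-year loss.* It was set for the three-month TUG.

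**Conclusion.** The point holds for the QALY and hence for the ICER. The GEE reason for not imputing does not cover a per-patient one-year QALY compared by bootstrap, and following the text would by default leave out patients without a full SF-36 series, against the declared intention-to-treat principle. The size is about 16 to 17 of 110 patients if the 15% carries over to one year, and more if retained patients miss forms. The possible bias ranges from none to about one standard error of the QALY difference in the assumed scenarios, and its direction cannot be stated from the documents. The insurer and therapist costs are not unavoidably lost. The matter concerns a secondary objective and does not touch the TUG analysis. It should be put right before the economic data are analysed.

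**What to change.** In Primary and secondary outcomes, limit the no-imputation sentence to outcomes analysed by GEE.

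In Healthcare costs and cost-effectiveness, add wording such as: *The cost-utility analysis includes all randomized patients. Insurer and physical therapist costs are retrieved to 12 months for every patient, including those who leave or are withdrawn, where consent allows. Missing SF-36 utilities and residual missing costs are multiply imputed by arm, using the preoperative SF-36 and TUG and all available follow-up values, and the imputation is combined with the bootstrap. The complete-case ICER is reported as a sensitivity analysis.*

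The cost is a few sentences and some extra programming, with no new visits or patients; the record requests use the consent already planned. The downside is that multiple imputation in this form assumes data are missing at random given the observed values. The complete-case comparison shows how far the result depends on the handling of missing data, but it does not test that assumption.
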